**Statistical analyses**

There are no data to reliably predict for RGV the ratio of CSF C4h to plasma AUC0-12h values. We expect this ratio to be quite low. Our power calculation is therefore only a rough estimate. If we assume that PK values will be normally distributed within each *ABCB1* genotype group, a standard deviation of 0.001 for the CSF-to-plasma ratio, and using Student’s t test, studying 17 individuals in each genotype group will allow us to detect with 80% power and an alpha of 0.05 a difference of 0.001 between *ABCB1* C/C and T/T genotype groups. Because we anticipate that not all participants will be evaluable, we will enroll 3 additional individuals in each of the genotype groups, for a total of 20 per genotype group.

The primary outcomes of interest will be ratios of the CSF RGV C4h value to the plasma RGV Cmax, Cmin and AUC0-12h values. If PK parameters are normally distributed within each genotype group, then genotype groups will be compared using Student’s t test. If PK parameters are not normally distributed within each genotype group, then genotype groups will be compared using nonparametric tests such as the Mann-Whitney U test.

1. **Privacy/Confidentiality Issues**

All laboratory specimens, evaluation forms, reports, and other records that leave the site will be identified by coded number only to maintain subject confidentiality. All records will be kept locked. All computer entry and networking programs will be done with coded numbers only.

1. **Follow-up and Record Retention**

Study records will be retained for at least 10 years.

**Appendix A:** Schedule of events

|  |  |  |  |  |  | Day |  |  |  |  |  |  |
| --- | --- | --- | --- | --- | --- | --- | --- | --- | --- | --- | --- | --- |
|  | Screen -365 to -1 | Screen -30 to -1 | 1 | 2 | 3 | 4 | 5 | 6 | 7 | 8 | 9 | 14 (±2) |
| **All subjects** |  |  |  |  |  |  |  |  |  |  |  |  |
| Informed consent | X |  |  |  |  |  |  |  | X |  |  |  |
| *ABCB1* genotype | X |  |  |  |  |  |  |  |  |  |  |  |
| Routine safety labs (creatinine, CBC with diff, platelet count, ALT, AST, alkaline phosphatase, bilirubin, creatinine kinase (CK)) |  | X |  |  |  |  |  | X |  |  |  |  |
| HIV serology |  | X |  |  |  |  |  |  |  |  |  |  |
| Urine or Serum pregnancy test (women only) |  | X | X |  |  |  |  |  |  |  |  |  |
| Take raltegravir 400 mg every 12 hours |  |  | X | X | X | X | X | X | X |  |  |  |

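### The primary test is chosen by an unspecified normality check on the raw CSF-to-plasma ratios; one log-scale analysis should be fixed in advance for all three ratios

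*Protocol*

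**What the plan says.** Under Statistical Considerations, Statistical analyses, the Protocol names three primary outcomes: CSF raltegravir at 4 hours divided by plasma Cmax, by plasma Cmin and by plasma AUC0-12h. The test depends on the data. Student's t test is used if the PK parameters are normally distributed within each genotype group. If they are not: "If PK parameters are not normally distributed within each genotype group, then genotype groups will be compared using nonparametric tests". The Mann-Whitney U test follows as an example, not as the only permitted choice.

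The sample size is worked out for the t test only. It assumes normality within each group and "a standard deviation of 0.001 for the CSF-to-plasma ratio". From this it concludes that "studying 17 individuals in each genotype group" gives "80% power and an alpha of 0.05" to detect "a difference of 0.001 between" the C/C and T/T groups. Then "we will enroll 3 additional individuals in each of the genotype groups", which brings each group to 20. On the size of the ratio the section says only "We expect this ratio to be quite low". It admits that no data reliably predict the ratio and calls the calculation a rough estimate.

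**The concern.** The rule lets the outcome data pick the primary test but does not say how. It names no normality test and no threshold. It does not say what happens when one group looks normal and the other does not, or when the three ratios point different ways. The fallback is a class of tests.

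The two branches do not answer the same question. The t test compares mean ratios; Mann-Whitney compares ranks. The three ratios share one numerator, the 4-hour CSF concentration, yet could be reported by different methods for no reason beyond sampling noise.

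The scale adds to this. Each outcome is a quotient of positive concentrations that is expected to be low, so skewness is plausible and a genotype effect is naturally read as a fold change. The SD and the difference are stated in raw ratio units without a mean, so the fold change the trial can detect cannot be recovered from the text.

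**Working it through.** **1. The Protocol's own figure.** Inputs from Statistical analyses: difference 0.001, SD 0.001, alpha 0.05, power 80%, equal groups. Sidedness is not stated; two-sided is assumed.
- Standardised difference: d = 0.001 / 0.001 = 1.0.
- Two-sample t test by noncentral t: n = 16.71 per group, rounded up to 17. Power at 17 is 0.807.
- One-sided power at 17 would be 0.886, so the two-sided reading is the one that reproduces the stated 80%.

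The figure reproduces. It is a statement about a 1 SD difference under a t test.

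**2. How often the rule takes each branch.** The Protocol names neither a normality test nor a distribution. Assumptions: lognormal ratios, 17 per group, Shapiro-Wilk at 0.05 in each group, Mann-Whitney if either group fails. With SD 0.001 and no genotype effect:

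| Assumed mean ratio | CV = 0.001 / mean | Switches to Mann-Whitney | Both groups pass |
|---|---|---|---|
| 0.001 | 100% | 96% | 4% |
| 0.002 | 50% | 65% | 35% |
| 0.003 | 33% | 41% | 59% |
| 0.005 | 20% | 23% | 77% |

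With truly normal data the rule still switches in about 10% of trials. In the middle of this range the branch taken is largely chance.

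If the three ratios are also assumed to be correlated at 0.5 to 0.8, they do not all take the same branch in 52% to 67% of null trials at CV 30% to 50%, and in 24% to 29% at CV 80%.

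**3. What the rule costs.** Log-scale SD = sqrt(ln(1 + CV²)). The true effect is set at 0.991 log-scale SD, which a log-scale t test detects with 80% power at 17 per group. Over CV 30% to 150%:
- Power of the two-stage rule: about 77% to 79%. Log-scale t test: 80% to 81%. The loss is about 1 to 3 points.
- Overall type I error of the two-stage rule: 0.051 to 0.059.
- The t test and Mann-Whitney disagree on significance in 7% to 25% of trials under the alternative (about 10% at CV 50%), so the branch can decide the conclusion.

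**4. Reading the power as a fold difference.** A difference of 0.001 is a ratio of (m + 0.001) / m for lower-group mean m. For m = 0.001, 0.002 and 0.005 this is 2.0, 1.5 and 1.2. Power of the two-stage rule for that difference at 17 per group depends on what else is assumed:
- Raw SD 0.001 in both groups (m from 0.001 to 0.01): 0.81 to 0.97.
- Constant CV, with SD 0.001 at the lower mean (m from 0.001 to 0.005): 0.63 to 0.74.

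The Protocol does not say which of these applies.

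**5. Detectable geometric mean ratio at 17 per group, 80% power.** Formula: exp(0.991 × sqrt(ln(1 + CV²))).
- CV 50%: exp(0.991 × 0.472) = 1.6
- CV 80%: exp(0.991 × 0.703) = 2.0
- CV 100%: exp(0.991 × 0.833) = 2.3

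**The case against.** The case against acting is that the measurable harm is small. The two-stage rule tracks a log-scale test to within a few points of power and barely moves the overall type I error. A normality criterion is common SAP content, and the SAP is not at hand. A single prespecified Mann-Whitney test would remove the data-driven choice equally well. All of that stands. It limits the weight of the point but does not remove it, because the choice of test from the data is itself written in the Protocol.

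Several stronger readings are tempting and are not supported:
- **That the power statement is wrong or meaningless.** It reproduces at 0.807 and is labelled rough.
- **That the plan suffers the power loss of a raw t test on skewed data.** Applied unconditionally, that test has roughly 77%, 70%, 67% and 58% power at CV 50%, 80%, 100% and 150%. The plan does not apply it unconditionally; it switches. Among samples that pass the check at CV 50%, the raw t test does slightly better than the log test (84% against 82%).
- **That the normal assumption implies many negative ratios.** With SD 0.001 it puts 15.9% below zero at a mean of 0.001 and 2.3% at 0.002, but only 0.13% at 0.003. The Protocol gives no mean.
- **That a rank analysis offers no effect size and cannot account for sex.** A Hodges-Lehmann shift and a stratified rank test do both.

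**Conclusion.** The point holds as an inexpensive improvement, not as an error that endangers the trial. The Protocol fixes a rule under which the primary comparison is settled by an unnamed check and an open fallback, possibly differently across three related ratios. At a CV near 50%, which test is run is largely chance. Under the assumptions in the working, the price is about 1 to 3 points of power, with overall type I error of 0.051 to 0.059.

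These sizes rest on lognormal ratios, Shapiro-Wilk at 0.05 in each group, and CVs that the Protocol does not supply. That the check runs on the raw scale is an inference, though a fair one: no transformation appears, and the SD and difference are in ratio units. The sample size of 17 evaluable per group is not called into question. What is missing from the power statement is a fold-difference reading and coverage of anything beyond the t-test branch.

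**What to change.** Replace the conditional rule with one primary analysis for all three ratios: a t test on log-transformed ratios, or a linear model on the log scale with sex, which the design already balances at 10 men and 10 women per genotype group (Schema; section 4.0.1). Report the T/T-to-C/C geometric mean ratio with its 95% CI. Keep Mann-Whitney as a sensitivity analysis only. Leave the sample size as it is, and add that 17 per group detects a geometric mean ratio of about 1.6, 2.0 or 2.3 for assumed CVs of 50%, 80% or 100%.

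The cost is wording; there are no extra participants or procedures. The small downside is that CSF values below the assay limit need a stated handling rule on the log scale. If many are expected, a single prespecified Mann-Whitney test with a Hodges-Lehmann estimate would also remove the data-driven choice.

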# Appendix C: Specimen Collection and Processing

| **Assay/Procedure** | Tube Type or Specimen Type and Quantity | Derivative | Processing Instructions | Aliquots/Storage | Shipping Address, Frequency, and Other Instructions |
| --- | --- | --- | --- | --- | --- |
| Plasma raltegravir assaysa | Whole blood in 10 mL K3 EDTA tube: 1 tube per scheduled draw time. | Plasma | Place sample on ice promptly after collection. Within 1 hour spin blood at 800xg for 10 minutes at 4OC; remove plasma and freeze 4 equal aliquots (at least 1 mL each) at ‑70°C. | 4 equal aliquots (at least 1 mL plasma per cryovial). Store immediately at ‑70°C. | One aliquot from each timepoint will be batch shipped to:  [name].  Antiviral Laboratory Director  Lab Contact:  [name]  Division of Clinical Pharmacology  University of Alabama at Birmingham  [name]  [name]  [name]  [contact]  [contact]  Include ample dry ice to ensure frozen delivery of samples on next business day. Notify laboratory when shipment is placed.  The remaining aliquots will continue to be stored at -70OC. |
| **CSF raltegravir assays**a | 15 mL Cerebrospinal fluid collected on ice. | CSF | Place CSF tube promptly on ice. Pipette at least 5 mL UNSPUN CSF (at least 1 ml per tube) directly into at least 5 separate 2-mL Sarstedt Micro tubes (cryovials, catalogue no. 72.694.006). Label tubes “UNSPUN”  Spin the remaining CSF (at least 6 mL) at 800x*g* for 10 minutes at 4OC in a 15 mL conical tube. Pipette supernatant into at least 5 separate cryovials (at least 1 mL per tube). Label tubes “SPUN”. Take care not to disturb the pellet (even if no pellet is visible) | 10 equal aliquots of CSF (at least 5 unspun and 5 spun). Store immediately at ‑70°C. | Two SPUN aliquots from each timepoint will be batch shipped to:  [name].  Antiviral Laboratory Director  Lab Contact:  [name]  Division of Clinical Pharmacology  University of Alabama at Birmingham  [name]  [name]  [name]  [contact]  [contact] |
| ***ABCB1* genotypeb** | Whole blood in 10 ml K3 EDTA tube |  | Collect whole blood into Sarstedt K3 EDTA Monovette. Either store within 12 hours at ‑70°C, or deliver ambient to Vanderbilt DNA Resources Core.  Description:  Sarstedt K3 EDTA Monovette  Product Number: 01.1605.100  [contact] | N/A | Vanderbilt DNA Resources Core  Attn: [name]  [name]  Vanderbilt University, Medical Center  [name]  [contact]  [contact]  E-mail: [contact] |
| **CBC with diff and platelets** | Whole blood in 4 mL purple-top EDTA tube |  | Send in real-time to clinical lab for assay |  | LabCorp |
| **Creatinine, ALT, AST, alkaline phosphatase, bilirubin, Creatinine Kinase (CK)** | Whole blood in 8.5ml red marble-top tube |  | Send in real-time to clinical lab for assay |  | LabCorp |
| **HIV Elisa** | 8.5ml red marble-top tube |  | Send in real-time to clinical lab for assay |  | LabCorp |
| **CSF total protein , cell count** | Unspun CSF, 2 mL. |  | Send in real-time to clinical lab for assay |  | Vanderbilt Univ Med Ctr  Diagnostic Lab  [name]  Deliver to lab immediately  Cell count test code (CSF) CPT code 89051  Protein test code (SFP) CPT code 84157 |
| **PBMC raltegravir assays**a | Whole blood in 10 mL K3 EDTA tube: 2 tubes per scheduled draw time. |  | Whole blood for PBMCs will be promptly placed in an ice bath. PBMCs will be isolated within 1 hour at 4OC and counted with a hemacytometer. Cell density will be adjusted to a concentration of 2 x 106 cells/ml with ice-cold phosphate buffered saline, then aliquotted into as many 1 mL aliquots as possible, and promptly placed at -80OC. Discard the final aliquot if it has less than 2 x 106 cells/ml. |  | Two PBMC aliquots from each timepoint will be batch shipped to:  [name].  Antiviral Laboratory Director  Lab Contact:  [name]  Division of Clinical Pharmacology  University of Alabama at Birmingham  [name]  [name]  [name]  [contact]  [contact] |

a Raltegravir in CSF and plasma will be assayed by GC/MS assay.

b Genomic DNA will be extracted from whole blood using PUREGENE (Gentra Systems, Inc., Minneapolis, MN). Genotyping will be accomplished with the ABI PRISM 7900 HT Sequence Detection System (Applied Biosystems, Inc., Foster City, CA), using customized TaqManTM assays.

**Appendix D:** Upper limit weight cut-off for study participation (body mass index = 30)

| **Feet** | | **Inches** | | **Weight cutoff (pounds)** | |
| --- | --- | --- | --- | --- | --- |
| 4 | ft | 0 | in | 98.3 | lbs |
|  | ft | 1 | in | 102.5 | lbs |
|  | ft | 2 | in | 106.7 | lbs |
|  | ft | 3 | in | 111.0 | lbs |
|  | ft | 4 | in | 115.4 | lbs |
|  | ft | 5 | in | 119.9 | lbs |
|  | ft | 6 | in | 124.4 | lbs |
|  | ft | 7 | in | 129.1 | lbs |
|  | ft | 8 | in | 133.8 | lbs |
|  | ft | 9 | in | 138.6 | lbs |
|  | ft | 10 | in | 143.6 | lbs |
|  | ft | 11 | in | 148.5 | lbs |
| 5 | ft | 0 | in | 153.6 | lbs |
|  | ft | 1 | in | 158.8 | lbs |
|  | ft | 2 | in | 164.0 | lbs |
|  | ft | 3 | in | 169.4 | lbs |
|  | ft | 4 | in | 174.8 | lbs |
|  | ft | 5 | in | 180.3 | lbs |
|  | ft | 6 | in | 185.9 | lbs |
|  | ft | 7 | in | 191.6 | lbs |
|  | ft | 8 | in | 197.3 | lbs |
|  | ft | 9 | in | 203.2 | lbs |
|  | ft | 10 | in | 209.1 | lbs |
|  | ft | 11 | in | 215.1 | lbs |
| 6 | ft | 0 | in | 221.2 | lbs |
|  | ft | 1 | in | 227.4 | lbs |
|  | ft | 2 | in | 233.7 | lbs |
|  | ft | 3 | in | 240.0 | lbs |
|  | ft | 4 | in | 246.5 | lbs |
|  | ft | 5 | in | 253.0 | lbs |
|  | ft | 6 | in | 259.6 | lbs |
|  | ft | 7 | in | 266.3 | lbs |
|  | ft | 8 | in | 273.1 | lbs |
|  | ft | 9 | in | 280.0 | lbs |
|  | ft | 10 | in | 286.9 | lbs |
|  | ft | 11 | in | 294.0 | lbs |
| 7 | ft | 0 | in | 301.1 | lbs |
|  | ft | 1 | in | 308.3 | lbs |

**On-line BMI calculator available at** [**http://www.nhlbisupport.com/bmi/**](http://www.nhlbisupport.com/bmi/)

# Appendix E: Pharmacokinetic (PK) Evaluations

Subjects will arrive at the VICTR- Clinical Research Center (VICTR-CRC) before 6 PM the evening prior to the PK sampling visit. Study drugs will be given at the same time as the subject’s usual dose. Subjects should take their scheduled doses of study drugs AT THE SAME TIMES for at least 2 days prior to the PK sampling visit. This should ideally be at 7 AM and 7 PM. The subject should then take the RGV at the same time (7 AM) and the second dose 12 hours later (7 PM).

After the participant takes the observed dose of RGV on the evening of day 6, the participant will leave VICTR-CRC to return at 6 AM the next morning for a 24-hour VICTR-CRC stay. Under rare circumstances the participant may stay in VICTR-CRC overnight on Day 6.

Before initiating the evaluations listed below, study personnel should review the daily medication log with the subject and conduct a pill count. If the subject meets adherence requirements, the plasma and PBMC PK evaluations can be conducted.

If the subject does not meet adherence requirements, no sample should be drawn. If adherence requirements are not met, study drug should be discontinued and the subject should be taken off study after completion of the safety follow-up visit.

All plasma and PBMC PK samples must be drawn ideally at the times listed below. The actual collection time must be recorded on the case report form.

*PK Sampling on Days 6 and 7 in GCRC:*

| Hour | Activity | Specimen Drawn |
| --- | --- | --- |
| **DAY 6** |  |  |
| 6:00 PM | Arrive at VICTR-CRC. Venipuncture for safety labs. |  |
| 6:30 | Snack |  |
| 7:00 PM | Administer raltegravir 400 mg PO. Record administration time. Collect medication diary. |  |
| 7:00 PM | Leave VICTR-CRC |  |
| **DAY 7** |  |  |
| -1 (6:00 AM) | Arrive at VICTR-CRC |  |
| -1 | Vital Signs |  |
| -0.5 (6:30 AM) | Indwelling venous catheter insertion |  |
| -0.25 (7:45 AM) | Baseline plasma PK sample | 10 mL EDTA |
| 0 (7:00 AM) | Administer raltegravir 400 mg PO **EXACTLY 12 HOURS AFTER PREVIOUS DOSE**; start clock; record administration time; document hour and day of last food. |  |
| 1 | plasma PK sample | 10 mL EDTA |
| 2 | plasma PK sample | 10 mL EDTA |
| 3 | plasma PK sample | 10 mL EDTA |
| 3 | Light regular meal |  |
| 4 | Lumbar puncture for CSF | 15 mL CSF |
| 4 | plasma PK sample | 10 ml EDTA |
| 4 | PBMC PK sample | 20 mL EDTA |
| 5 | plasma PK sample | 10 mL EDTA |
| 6 | plasma PK sample | 10 mL EDTA |
| 8 | plasma PK sample | 10 mL EDTA |
| 8 | Regular diet ad lib hereafter |  |
| 12 | plasma PK sample | 10 mL EDTA |
| 16 | plasma PK sample | 10 mL EDTA |
| **DAY 8** |  |  |
| 20 (3:00 AM) | plasma PK sample | 10 mL EDTA |
| 24 (7:00 AM) | plasma PK sample | 10 mL EDTA |
| 24 | PBMC PK sample | 20 mL EDTA |
| 24.25 | Remove venous catheter |  |
| 24.25 | Discharge subject from VICTR-CRC |  |
| **DAY 9** |  |  |
| 48 (7:00 AM) | plasma PK sample | 10 mL EDTA |
| 48 | PBMC PK sample | 20 mL EDTA |

IN-PATIENT MENU

A light meal of subjects’ choice will be provided 3 hours after the study drug is given.

NOTE: Subjects are NOT to be given grapefruit or grapefruit juice.

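### The Day 7 baseline plasma sample in Appendix E carries a clock time one hour off its nominal time, which places it 45 minutes after the dose; a minor correction, but to the only pre-dose sample

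*Protocol*

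**What the plan says.** The Day 7 table in Protocol Appendix E gives some rows both an hour relative to dosing and a clock time. Arrival is "1 (6:00 AM) | Arrive at VICTR-CRC" and catheter placement is "0.5 (6:30 AM) | Indwelling venous catheter insertion", both with a minus sign before the hour. The next row is the baseline draw, "0.25 (7:45 AM) | Baseline plasma PK sample | 10 mL EDTA", again with a minus sign. The row after that is the dose, "0 (7:00 AM) | Administer raltegravir 400 mg PO".

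The text above the table gives the same morning dose time: "The subject should then take the RGV at the same time (7 AM) and the second dose 12 hours later (7 PM". On sample timing it says "All plasma and PBMC PK samples must be drawn ideally at the times listed below", and it requires the actual collection time to be recorded on the case report form. The dose row asks for the administration time to be recorded as well.

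Section 10 (Statistical Considerations) makes the ratios of CSF C4h to plasma Cmax, Cmin and AUC0-12h the primary outcomes.

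**The concern.** The hour and the clock time in the baseline cell cannot both be right, and they fall on opposite sides of the dose. The cell is in the table that staff work from on the sampling day. No sentence says outright that the baseline sample comes before the dose; the reader learns this only from the negative hour, the row's name and its position.

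This is the only pre-dose plasma sample in the schedule, since the Day 6 draw is for safety laboratory tests. It supplies the concentration at the start of the AUC0-12h interval and is one of two trough values that could serve as Cmin, the other being the 12 h sample. Both parameters are denominators of primary ratios. Each participant has one sampling day and one lumbar puncture, so a missed pre-dose draw cannot be repeated within the protocol.

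**Working it through.** **1. Clock check.** Inputs are the rows of the Appendix E table for Days 7 to 9 that carry both labels. Formula: expected clock time = 7:00 AM + nominal hour.

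| Row | Nominal hour | Expected | Printed | Difference |
|---|---|---|---|---|
| Arrival | -1 | 6:00 AM | 6:00 AM | 0 min |
| Catheter | -0.5 | 6:30 AM | 6:30 AM | 0 min |
| Baseline sample | -0.25 | 6:45 AM | 7:45 AM | **+60 min** |
| Dose | 0 | 7:00 AM | 7:00 AM | 0 min |
| Plasma, Day 8 | 20 | 3:00 AM | 3:00 AM | 0 min |
| Plasma, Day 8 | 24 | 7:00 AM | 7:00 AM | 0 min |
| Plasma, Day 9 | 48 | 7:00 AM | 7:00 AM | 0 min |

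The printed baseline time relative to the dose is 7:45 - 7:00 = +45 min, or +0.75 h, against a nominal -15 min. The two Day 8 rows read "20 (3:00 AM) | plasma PK sample | 10 mL EDTA" and "24 (7:00 AM) | plasma PK sample | 10 mL EDTA". A clock time of 7:45 AM would equal -0.25 h only for an 8:00 AM dose. That contradicts the dose row, the text, and the instruction that this dose follow the 7:00 PM Day 6 dose by exactly 12 hours.

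**2. What would be lost if the clock time were followed.** The plasma samples in the dosing interval would then fall at +0.75, 1, 2, 3, 4, 5, 6, 8 and 12 h. There would be no value at time zero. A trough at 12 h would remain.

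**3. Effect on AUC0-12h if the late value were also entered as time zero.** The documents hold no raltegravir concentrations, so this step is illustrative. Concentration rises from 0 to 1 h, so the first trapezoid is linear. Replacing C(0) by C(0.75) adds an area of

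0.5 × 1 h × [C(0.75) - C(0)].

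The relative error is that area divided by AUC0-12h, computed by the linear/log trapezoidal rule at 0, 1, 2, 3, 4, 5, 6, 8 and 12 h.

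*Model A (assumed): one compartment, steady state, 12 h interval, terminal half-life 6 to 12 h, absorption rate ka 1 to 2 per h.* With λ = ln 2 / half-life,

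C(t) ∝ ka/(ka - λ) × [e^(-λt)/(1 - e^(-12λ)) - e^(-ka·t)/(1 - e^(-12ka))].

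| Half-life, ka | C(0) | C(0.75) | Ratio | AUC0-12h | AUC error |
|---|---|---|---|---|---|
| 12 h, 1 per h | 1.061 | 1.531 | 1.4 | 17.23 | 0.5 × 0.470 / 17.23 = 1.4% |
| 6 h, 2 per h | 0.354 | 1.061 | 3.0 | 8.49 | 0.5 × 0.707 / 8.49 = 4.2% |

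The other two combinations of these values lie between.

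*Model B (assumed): the same, plus a fast disposition phase with half-life 0.8 to 1.5 h, the slow phase carrying 5% to 20% of the disposition coefficient.* The +0.75 h value is then about 3 to 33 times the trough, and AUC0-12h is overstated by about 4% to 20%.

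The CSF-to-AUC ratio would be understated to match: 1 - 1/1.014 = 1.4% and 1 - 1/1.042 = 4.0% at the ends of model A, and up to 1 - 1/1.20 = 17% in model B.

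**The case against.** The strongest reply is that nobody is likely to be misled. The hour column says -0.25, the row is named as the baseline, it stands between catheter placement and the dose, and the schedule's clock starts at the dose. To follow the printed time, staff would have to pass over a row, give the dose, and then draw a sample labelled with a negative hour. If that did happen, the recorded draw and dose times would show it. This largely stands: the error is probably typographical and likely to be noticed. What remains is that recorded times would reveal a late draw but would not recover the pre-dose value.

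A reader might infer that Cmin would be wrong by the full ratio of the +0.75 h value to the trough. The documents do not support this. Section 10 defines Cmin as the minimum plasma concentration; a value drawn during absorption would exceed the trough and would not be chosen, and the 12 h sample still supplies the minimum. Cmin would change only if the missed pre-dose value had been lower than the 12 h value.

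A reader might also infer a fixed, sizeable inflation of AUC0-12h. That needs a second error, because an analyst would have to enter a sample recorded after the dose as time zero. Its size depends on a model that the documents do not provide.

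Finally, a reader might infer a bias between genotypes. The misprint applies equally to C/C and T/T participants, and nothing suggests that draw times would differ by genotype.

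**Conclusion.** The contradiction is certain and exact: 60 minutes between the two labels, with the printed clock time 45 minutes after the dose. A pre-dose draw is clearly intended.

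The consequence is conditional. If the clock time is followed, the time-zero concentration for AUC0-12h and one of the two trough candidates are lost. If the late value is also treated as time zero, AUC0-12h is overstated in every case calculated, by about 1% to 4% under model A and up to about 20% under model B. Both ranges rest on assumed kinetics, not on data in the protocol. The sample-size calculation is not affected. This is a minor correction, worth making because it costs almost nothing and protects a sample that cannot be repeated.

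**What to change.** - In the Appendix E Day 7 table, make the clock time agree with -0.25 h: 6:45 AM for a 7:00 AM dose.
- Add to that row that the baseline sample is drawn before the dose.
- For anyone already sampled, compare the recorded draw time with the recorded dose time. Place the sample at its actual time, do not treat a post-dose draw as time zero, and regard the time-zero value as missing in that participant.

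The cost is one table cell, a few added words, a note to the research unit and, if sampling has begun, a check of times that the case report form already holds.
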